**Results::**

The primary efficacy endpoint will be analysed as a time-to-event outcome. A vaccine will be considered successful if its estimated efficacy is greater than 50% and has sufficient precision to rule out that true efficacy is less than 30%. This will require approximately 150 total endpoints, that is, cases of confirmed Marburg virus disease, per vaccine/comparator combination. Interim analyses will be conducted after 50 and after 100 events. Statistical analysis of the trial will be blended across the different types of designs. Under the assumption of a 6-month attack rate of 1% of the participants in the placebo arm for both the individually and cluster-randomized populations, the most likely sample size is about 20,000 participants per arm.

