## Results

### VE analysis

The primary efficacy endpoint will be analysed as a time-to-event outcome, including only those events that occur 10 days after the final vaccination dose. Such a gap of 10 days is chosen to allow time for the vaccination series to take effect and to reduce the chance of including events occurred prior to the vaccination due of the incubation period for Marburg. All participant-level failure (diagnosis with disease) and censoring events are reported relative to the time of randomization. The time of virologically confirmed (i.e. laboratory-confirmed) MARV disease is the earliest time of reported qualifying MARV disease symptoms that occur within 10 days of virological confirmation of MARV infection. Participants’ follow-up times will be right censored at the time of last contact at which endpoint status was assessed. Cox proportional hazards regression will be used for analysis. VE, measured by one minus the hazard ratio (vaccine versus placebo/comparator), will be the effect measure. Inference will be based on a one-sided logrank test of H_0_
^benefit^: VE ≤ 0.30, using an O'Brien-Fleming boundary for early termination that preserves an experimental (one-sided) 0.025 error rate; the alpha levels would be one-sided 0.0003 at 50 events and one-sided 0.0069 at 100 endpoints, where the remainder of the (one-sided) 0.025 error rate would be spent at the final analysis. Using these O'Brien-Fleming criteria after 50 and 100 events, benefit is established when estimated VE is ≥80% and ≥59%, and lack of benefit, that is, ruling out the target VE of 60% for which the trial has 90% power, is established when estimated VE is ≤−6% and ≤34%, respectively. When estimating VE against infection, the outcome would be infection as measured by time to seroconversion, using interval censoring methods for the estimand. In this case, the operating characteristics of the statistics would be the same as described above.

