### Study sample size for a mixture of individually and cluster-randomized designs

For those designs involving cluster randomization, the number of events needed to assess efficacy and sample sizes would be increased to account for the correlation within clusters. While the intraclass correlation coefficient (ICC) parameter for continuous and binary outcomes is commonly used, it is not easily extended to time-to-event outcome settings because of the presence of censoring (e.g. losses-to-follow-up, end-of-study administrative censoring).^
15
^ It has been shown that ICC estimators based on censoring indicators or observed event times can be negatively biased.^16,17^

One way to account for the clustering effect is using an ICC based on the binary event indicator and to inflate the events required by the usual design effect that equals 1 + (*m −* 1) ICC, where *m* is the average cluster size.^
18
^ For the Ebola ring vaccination trial in Guinea, the average ring size was about 80, and the ICC was about 0.05, resulting in a design effect of about 4. Thus, 600 total events would be needed for the design above, resulting in 150 effective events. For mixtures of individually and cluster-randomized designs, the target number of events will be the total number of effective events.

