### Blending of analysis across designs

For the primary outcome, results will be combined across individually and cluster-randomized designs using a marginal proportional hazards model. We will assume that these different designs represent independent sources of evidence. Compared to the mixed-effects modelling approaches, the marginal model offers a simple marginal interpretation of intervention effects and avoids the need to specify the correlation structure among the observations. Stratified marginal models will be considered to allow differential baseline hazard functions across studies. The marginal model will be fitted under a ‘working independence’ assumption and inference will be performed using the robust sandwich variance estimator which ensures valid inference when there is a within-cluster dependence in event times.^
19
^ Alternative randomization-based inference methods could also be used^
20
^ that can account for design features (e.g. stratified randomization) in a straightforward way through restricted permutation. Another commonly used approach to combine estimates from different studies is through the use of meta-analysis approaches. When analysing censored data with a Cox proportional hazards model, the inverse-variance estimator based on the fixed-effects meta-analysis method is asymptotically equivalent to the maximum partial likelihood estimator using pooled individual-level data under a stratified model which assumes a different baseline hazard function across studies.^
21
^

It is important to note that the estimand for VE under individual randomization is in general different from the one under cluster randomization, with the former targeting direct vaccine effectiveness and the latter total vaccine effectiveness.^
22
^ (Although when direct effectiveness is high or clustering low, i.e. ICC is near zero, the two are nearly identical.) Without differentiating the two, the parameter represents a weighted average. One could parameterize the total effect as the sum of direct effects and indirect effects in the model. The availability of data from both individual and cluster-randomized trials permits the estimation of both by including an interaction term between the treatment variable and an indicator variable that takes value 1 if data are from the cluster-randomized trials and 0 otherwise.

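### The logrank test and the interim VE limits at 50 and 100 events hold only for independent events and are not reconciled with the pooled analysis that admits cluster-randomised rings

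*Protocol article*

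**What the plan says.** Under VE analysis, a section not restricted to any one design, the protocol article states: "Inference will be based on a one-sided logrank test" of the hypothesis that VE is at most 30%, with an O'Brien-Fleming "boundary for early termination that preserves an experimental (one-sided) 0.025 error rate". It then fixes the looks: "the alpha levels would be one-sided 0.0003 at 50 events and one-sided 0.0069 at 100 endpoints". The levels are turned into limits on the point estimate: "after 50 and 100 events, benefit is established when estimated VE is ≥80% and ≥59" per cent. Lack of benefit is declared at an estimated VE of −6% or below and 34% or below at the same two looks. The Abstract (Results) repeats the timing: "Interim analyses will be conducted after 50 and after 100 events".

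Three other places bear on this:

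- Figure 1 makes whole clusters the unit of randomisation in design 2. The text after it says that the platform blends the designs.
- The section on sample size for a mixture of designs inflates the events by 1 + (m − 1) × ICC and says: "For mixtures of individually and cluster-randomized designs, the target number of events will be the total number of effective events".
- The section on blending of analysis combines the primary outcome across individually and cluster-randomised designs in a marginal proportional hazards model, where "inference will be performed using the robust sandwich variance estimator".

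**The concern.** One primary outcome has two stated inferences. The alpha levels and the stopping limits are attached only to the logrank test, whose usual variance treats events as independent. The sandwich analysis comes later, with no statement that it replaces the logrank test at the interim looks.

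The effective-event conversion is worded for the target number of events. Nothing says that the looks at 50 and 100 events, or the VE limits used there, are on that scale.

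This matters because the limits are thresholds on the estimate. Under working independence, the sandwich changes the standard error and leaves the estimate where it is. It therefore cannot protect a rule that declares benefit once estimated VE reaches 59% at 100 events. If those are 100 raw events from cluster-randomised rings with a design effect of 4.95, they carry the information of about 100 / 4.95 = 20 independent events. The limit is then far too easy to cross by chance in either direction, and correcting the final event target does not undo a stop already made.

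**Working it through.** **Inputs from the protocol article.** Null VE 30% (HR 0.70), target VE 60% (HR 0.40), 1:1 allocation, 150 events, one-sided levels 0.0003 and 0.0069 (z = 3.432 and 2.462), ring size about 80, ICC about 0.05.

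**1. Reproduce the plan's figures under independence.** With d events split as expected under hazard ratio h, SE(h, d) = √((1+h)/(dh) + (1+h)/d) = (1+h)/√(dh).

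- Benefit limit: solve ln(0.70/h) = z × SE(h, d). At d = 50, h = 0.183 (1.342 = 3.432 × 0.391), so VE is 81.7%. At d = 100, h = 0.407 (0.543 = 2.462 × 0.2205), so VE is 59.3%. Stated: 80% and 59%.
- Lack-of-benefit limit: solve ln(h/0.40) = z × SE(h, d). At d = 50, h = 1.056, so VE is −5.6%. At d = 100, h = 0.661, so VE is 33.9%. Stated: −6% and 34%.
- Power at 150 events (Freedman form, HR ratio 0.40/0.70 = 0.571): √150 × 0.429/1.571 = 3.34, and Φ(3.34 − 1.96) = 0.916. Stated: about 90%.

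The stated figures come back, within 2 points, from a standard error that assumes independent events.

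**2. Design effect.** The article's inputs give 1 + 79 × 0.05 = 4.95, while its text says about 4. Both are carried as a range. The share f of events from cluster-randomised rings is not given, so 25%, 50% and 100% are assumed. The variance of the log hazard ratio is multiplied by V = 1 − f + f × DE:

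- f = 25%: V = 1.75 to 1.99
- f = 50%: V = 2.50 to 2.98
- f = 100%: V = 4.00 to 4.95

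**3. Apply the stated limits at 50 and 100 raw events.**

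False benefit, true HR 0.70:
- Look 1: SE = 1.7/√35 = 0.287; z = ln(0.70/0.20)/0.287 = 4.36.
- Look 2: SE = 1.7/√70 = 0.203; z = ln(0.70/0.41)/0.203 = 2.63.

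Wrong lack of benefit, true HR 0.40:
- Look 1: SE = 1.4/√20 = 0.313; z = ln(1.06/0.40)/0.313 = 3.11.
- Look 2: SE = 1.4/√40 = 0.221; z = ln(0.66/0.40)/0.221 = 2.26.

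Each z is divided by √V. For example, false benefit at look 2 with V = 4.95 is 2.63/2.225 = 1.18, a probability of 11.8%. The two looks are combined as bivariate normal with correlation √(50/100) = 0.707.

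| Share of events from rings | False benefit by look 2, true VE 30% | Wrong lack of benefit by look 2, true VE 60% |
|---|---|---|
| 0 (independent) | 0.4% | 1.2% |
| 25% | 2.3–3.1% | 4.7–6.0% |
| 50% | 4.9–6.5% | 8.6–10.8% |
| 100% | 9.8–12.5% | 15.1–18.3% |

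A simulation of rings of 80 with gamma-distributed ring risk, ICC 0.05 and 1% control risk gives the same order. For 25%, 50% and 100% from rings, false benefit is 4%, 8% and 16% (0.7% if independent) and wrong lack of benefit is 5%, 9% and 16% (0.9% if independent).

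**4. The sandwich test.** At a single final analysis (440 rings of 80 per arm, about 600 events), the simulated one-sided type I error is 0.027 with the sandwich variance and 0.190 with the naive variance. A second simulation, with interim looks, gives about 3.5–4% for the sandwich test.

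**The case against.** The strongest reply is that the plan does not ignore clustering. The blending section gives the analysis for exactly this case, and a specific section is naturally read as governing a general one. The logrank test is the score test of the Cox model named beside it, so the change is mainly one of variance. The sample-size section for individual randomisation places the looks at 1/3 and 2/3 of events. Taken with an effective-event target of 150, that gives 50 and 100 effective events. The article prefers individual randomisation, calls cluster randomisation less likely to be selected, and says that the blended analysis needs further investigation. Fine details of information timing usually belong in an analysis plan that is not shown.

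Much of this stands. A reader might infer that the trial's 0.025 error rate fails, with a type I error of 20–24%. The documents do not support that. The figure (0.200 at design effect 4, 0.237 at 4.95) needs the naive logrank test at every look and all events from cluster-randomised rings, contrary to the blending section.

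What the reply does not remove is the interim rule. The 1/3 and 2/3 wording sits in the individually randomised section. Elsewhere the counts are plain cases: the Conclusion treats past outbreaks of 374 and 154 cases as passing the threshold of 150. Choosing the sandwich variance does not alter a limit on the point estimate. Nor is this a detail left to a later document, because the article itself prints the counts and limits under a heading that covers all designs.

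**Conclusion.** The point holds in a limited form. The test, looks and VE limits under VE analysis rest on independent events and are not reconciled with the effective-event target or the sandwich analysis that apply once cluster-randomised data are pooled. The final pooled test under the blending section is not itself invalid.

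The harm arises if the printed limits are used at 50 and 100 raw events. At the assumed ring shares, false benefit is then roughly 5 to 30 times its value under independence (2.3/0.4 to 12.5/0.4), and wrong lack-of-benefit stopping roughly 4 to 15 times (4.7/1.2 to 18.3/1.2).

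These sizes rest on three assumptions: the share of events from cluster-randomised rings, an ICC and ring size carried over from the Ebola ring trial, and the design effect acting as a variance multiplier on the log hazard ratio. The 100% row is an upper case that the article itself makes unlikely. If no cluster-randomised data enter, this problem does not arise.

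**What to change.** Under VE analysis, state that when any cluster-randomised data enter the comparison:

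- the one-sided test of VE at most 30% is the sandwich-variance test from the marginal Cox model, with the ring or transmission unit as the cluster, at every look;
- the interim looks occur at 1/3 and 2/3 of the effective (robust-variance) information;
- the benefit and lack-of-benefit boundaries are both applied on the robust z scale;
- the printed VE limits and the counts of 50 and 100 apply to individually randomised events, for which the logrank test stays.

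Match the Abstract.

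The z scale is safer than keeping the VE limits and relabelling the counts as effective events, because that count depends on the assumed design effect. If 600 raw events were counted as 150 effective on a design effect of 4 when it is 4.95, fixed limits would give an overall one-sided error of about 0.037–0.041.

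The change is wording only, since the sandwich analysis is already planned. The cost is later interim looks when rings contribute. If all events came from cluster-randomised rings, the looks would move from 50 and 100 to about 200 and 400 raw events at a design effect of 4, or 248 and 495 at 4.95.

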## Methods

### Operating characteristics of the trial design

A core protocol approach will be used, allowing multiple vaccine candidates to be tested against a shared placebo/control group. The primary objective of the trial will be to evaluate the effect of each vaccine on the rate of virologically confirmed MARV disease, regardless of severity. In some cases, it may also be possible to evaluated MARV infection as a co-primary outcome. Although the study may lack power for formal statistical inference about VE against severe disease or death due to MARV disease, these secondary endpoints will be evaluated and reported for each vaccine. Additional exploratory endpoints will include VE between the first and second dose, for two-dose vaccines. Infecting viruses will be sequenced as much as possible to assess the influence of virus clades and evolution on transmissibility, virulence and VE. A subset of trial participants will provide periodic blood samples. Immune markers measured from participants in this immunogenicity subset will be used to assess immune correlates of risk and protection, and help with the assessment of VE against infection.

The trial is endpoint-driven, as the main analysis for each vaccine arm versus the concurrent shared placebo/control arm is triggered by the occurrence of a total of 150 cases of MARV disease across these two arms. While results from the main analysis will be reported, blinded follow-up will continue to evaluate safety and duration of immunity. This fixed number of 150 endpoints provides 90% power to rule out the hypothesis that VE is ≤ 30%, when the true VE is ≥ 60%, where statistical significance would be achieved if the estimated VE were ≥ 50%. In the setting of COVID-19 vaccines, such results would meet or exceed the World Health Organization-Food and Drug Administration (FDA) established threshold for worthwhile VE.

A global data monitoring committee will regularly review the accumulating safety results and major endpoint results. Different candidate vaccines may be available or suitable to enter the trial at different calendar times. Using a shared placebo/control group and a common core protocol to evaluate multiple candidate vaccines in the trial, resources allocated to the evaluation of each candidate vaccine will be judiciously saved while a high standard of scientific rigour and efficiency is ensured.^
10

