**Table 1. table1-17407745221110880:** Required total sample size, expected study duration (in months).

Accrual rate(month)	Expected study duration(months of outbreak time)	Analysis times (months ofoutbreak time)			Cumulative total number of participants(both arms)		
		First interim	Second interim	Final	First interim	Second interim	Final
1000	14.4	9.4	13.3	16.7	9,370	13,350	13,721
5000	6.6	4.2	6.0	7.8	20,771	24,248	24,248
10,000	4.9	2.9	4.4	5.9	29,292	29,292	29,292
20,000	3.8	2.1	3.4	4.7	33,873	33,873	33,873
30,000	3.4	1.8	3.0	4.2	36,124	36,124	36,124

To reduce the time to obtain reliable insights about VE, the study size should be as large as possible. The large number of sites at diverse geographical locales will smooth out uncertainty in projected MARV disease attack rates in specific locales during specific calendar time periods. To increase the reliability of results, all efforts will be made to minimize the occurrence of missing data. The occurrence of and reasons for missing data will be reported by randomization group.

In the event that design 1.a. was used to assess the VE against infection by recruiting cohorts of people with potential high exposure, but in the absence of an outbreak, then the trial outcome could be infection measured by seroconversion against MARV. This design would involve serial blood samples from trial participants, with an infection event defined as a significant rise in antibody for bracketing serum samples. Since the time of infection would be interval-censored, analysis would be carried out using survival analysis for such data.^
14
^ Since the primary goal of vaccination would be to prevent disease, a VE estimate based only on infection, at best, would be likely to support only an accelerated/conditional approval that would require additional post-licensure effectiveness study(ies); and at worst, it would serve only as a hypothesis-generating demonstration project.

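### The optional infection endpoint counts only seroconversion between paired sera, so infections that end in death or loss before the next bleed cannot be events, and VE against infection is biased if that share differs by arm

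*Protocol article*

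**What the plan says.** The main endpoint is virologically confirmed Marburg disease. Infection has a conditional role. The Abstract (Methods) says it could be the primary objective in some cases. The section Operating characteristics of the trial design says "it may also be possible to evaluated MARV infection as a co-primary outcome". Study sample size for individually randomized designs places it in high-exposure cohorts under design 1.a: "in the absence of an outbreak, then the trial outcome could be infection measured by seroconversion against MARV".

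For that endpoint, VE analysis states that "the outcome would be infection as measured by time to seroconversion, using interval censoring methods for the estimand", and adds that the operating characteristics are the same as those given for the disease endpoint. The sample size section describes serial blood samples, "with an infection event defined as a significant rise in antibody for bracketing serum samples".

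No section says that virologically confirmed disease, or death from Marburg disease, counts as an infection event. None says how death before the next sample is handled for this endpoint. On fatality, the article lists severe disease and death as secondary endpoints and notes that "the study may lack power for formal statistical inference about VE against severe disease or death due to MARV disease".

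**The concern.** An event defined by bracketing sera needs a second serum. Someone infected after a negative bleed who dies before the next one never supplies it. The interval-censored likelihood then sees a person who was negative at the last bleed and was not observed afterwards, that is, a censored observation. The infection itself ended the follow-up, so the censoring is informative, and standard interval-censoring methods assume that it is not. The same holds for a confirmed case lost before the next bleed.

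The result is also inconsistent within the plan. A laboratory-confirmed fatal infection is an event for the disease endpoint but not for the infection endpoint.

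If the loss is proportionally equal in both arms, the hazard ratio survives. If the vaccine changes fatality among the infected, it does not. A vaccine that lowers fatality keeps more of its infected participants alive to be counted, so it looks weaker and may meet the lack-of-benefit rule. A vaccine that raises fatality looks better than it is.

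**Working it through.** **Inputs from the article** (VE analysis; Study sample size for individually randomized designs): 150 events, equal allocation, null VE 30% (HR 0.7), target VE 60% (HR 0.4), one-sided 0.025, about 90% power, and lack of benefit at 100 events if estimated VE is at or below 34%. The article carries these over to infection, so 150 and 100 are read here as counts of infection events.

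**The plan's own figure.** The Schoenfeld form is power = Φ(√(150/4) × ln(0.7/HR) − 1.96). With HR 0.4 this is Φ(6.124 × 0.560 − 1.96) = Φ(1.467) = 92.9%. The Freedman form gives 91.6% and an exact conditional binomial test gives 88.4%. The stated 90% reproduces.

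**Effect of the event definition.** Let c0 and c1 be the shares of all infections, including mild and silent ones, that end in death or loss before a closing bleed, in the placebo and vaccine arms. Events are rare, so person-time hardly changes and each arm's observed event rate is its true rate times (1 − c):

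HR observed = HR true × (1 − c1)/(1 − c0).

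The documents give no values for c0 and c1. The table assumes a range, with true VE 60% and c1 half of c0, and puts each observed HR into the power formula above.

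| c0 / c1 | Observed HR | Expected VE | Power at 150 seroconversions |
|---|---|---|---|
| equal, any value | 0.400 | 60% | 93% |
| 10% / 5% | 0.4 × 0.95/0.90 = 0.422 | 57.8% | 87% |
| 20% / 10% | 0.4 × 0.90/0.80 = 0.450 | 55.0% | 77% |
| 30% / 15% | 0.4 × 0.85/0.70 = 0.486 | 51.4% | 61% |
| 50% / 25% | 0.4 × 0.75/0.50 = 0.600 | 40.0% | 15% |

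With a final critical value of 2.0, to allow for the interim looks, the last two powers are 59% and 15%.

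**Simulation check.** With 18,062 per arm, a 1% placebo attack rate per 6 months, and an assumed 3-month bleed interval and 12-month follow-up, the simulated VE is 60.2% at 20%/20%, 51.3% at 30%/15% and 40.3% at 50%/25%. These agree with the formula.

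**Lack of benefit at 100 events.** The standard error of ln HR is 2/√100 = 0.2, and VE ≤ 34% means HR ≥ 0.66.
- No bias: ln(0.66/0.40)/0.2 = 2.50, a probability of 0.6%.
- 50%/25%: ln(0.66/0.60)/0.2 = 0.48, a probability of about 32%.

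**Opposite direction, for illustration.** With true VE 30% (the null), c0 = 30% and c1 = 50%, the observed HR is 0.7 × 0.50/0.70 = 0.50. The expected VE is then 50%, which is the article's success threshold.

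**Equal loss.** No bias arises, but events accrue more slowly. At 20%/20%, 150 infections yield 150 × 0.80 = 120 seroconversions.

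**The case against.** The strongest reply is that the article never says a confirmed or fatal case counts as uninfected. One might infer it from the sentence that follow-up is "right censored at the time of last contact at which endpoint status was assessed". That sentence, however, follows the definition of confirmed disease and precedes the Cox model, so it governs the disease endpoint, where a confirmed fatal case is an event. This stands, and the point does not rest on that sentence. It rests on the bracketing-sera definition, under which an interval-censored analysis stops at the last negative serum.

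A second reply is that the article promises a fully pre-specified estimand and that a condensed article may leave such handling to the analysis plan. The estimand could indeed repair this. But the article itself fixes the event definition, names the method and asserts unchanged operating characteristics, and the general promise alters none of these.

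A third reply is that the endpoint is optional and its claims are already limited. Study sample size for individually randomized designs says that VE on infection alone would at best support accelerated or conditional approval and at worst generate hypotheses. Fatal confirmed cases still count for the disease endpoint. This also stands and limits the stakes.

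Finally, one might infer from the secondary endpoint "VE against severe disease or death due to MARV disease" that the plan expects vaccines to reduce fatality. It only evaluates that effect. Nor is c0 the fatality of diagnosed cases: its denominator is all infections, including the silent ones that serology is meant to find, so it may be small. At 10%/5% the result is close to nominal. For a vaccine that lowers fatality, the error is conservative for a claim of benefit.

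**Conclusion.** The concern holds in limited form. As worded, the infection endpoint cannot register an infection that ends in death or loss before the next bleed, even a virologically confirmed one. VE against infection is then biased whenever the share lost differs by arm, and the statement that the operating characteristics are unchanged does not hold in that case. With equal shares there is no bias.

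The size is not known from the documents. For a true VE of 60% and loss halved by the vaccine, it runs from about 2 points of VE (c0 = 10%, power about 87%) to 20 points (c0 = 50%, power about 15%, with about a one-in-three chance of a false lack-of-benefit signal at 100 events). These figures assume that decisions are taken on seroconversion counts.

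A reader might infer that VE against infection is certain to be badly distorted, or that at very high fatality an effective vaccine would appear harmful. The documents do not support either reading. They give no fatality figure, bleed interval or symptomatic fraction, and they assume no effect on death.

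The definition should be changed before any site uses infection as a primary or co-primary outcome, because a serum that was never drawn cannot be recovered later.

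**What to change.** In VE analysis and in Study sample size for individually randomized designs, define infection as the first of:
- virologically confirmed Marburg disease or virologically confirmed Marburg death, dated as for the primary endpoint; or
- seroconversion between bracketing sera.

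State that a confirmed case is not censored at the last negative serum. Analyse the resulting mix of exact and interval-censored times, and report seroconversion alone as a supportive analysis. Limit the statement on operating characteristics to this revised endpoint.

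The cost is endpoint wording and a slightly more complex model, which standard software can fit. Confirmed disease and Marburg death are already collected as primary and secondary endpoints. If every lost infection were confirmed, c0 and c1 would fall to zero and the 60% VE and roughly 90% power would be restored. Fatal infections that were never tested would still be missed, so deaths without virological confirmation should be reported by arm. If fatality proves equal in the two arms, the change does no harm.
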